#### Data collection

Baseline characteristics will include infant gestational age at birth, delivery mode, singleton or multiple births, birth weight, sex, APGAR score (1, 5, and 10 min after delivery), resuscitation measures during the first 30 min after birth, first blood gas, umbilical arterial and venous pH, standard base excess, and lactate. Information on vital signs (oxygen saturation, FiO_2_, and heart rate) will be collected 15 min before and after the procedure. Information on treatment with antibiotics, fluids, vasopressors, and early caffeine before the LISA procedure will be recorded. We will calculate the time from meeting the criteria for surfactant treatment until the procedure starts. We will also include maternal information regarding smoking status, diseases (diabetes mellitus, amnionitis as per the obstetrician, preeclampsia, and eclampsia), and antenatal administration of steroids, magnesium sulphate, indomethacin, and antibiotics, including timing.

A generic procedure description will be created for the clinician to use in the medical records to ensure that all information, including modified COMFORTneo score before the procedure, administration of atropine, early caffeine and naloxone, and indications for additional fentanyl administration and cumulated dosage, is recorded uniformly.

If the infant is discharged to a step-down unit, information will be retrieved from that unit.

#### Data management

Study data will be collected and managed using REDCap electronic data capture tools hosted at the Capital Region of Denmark.^25^ A password will protect access to the online forms and dataset, and infants will be identified by number only to protect confidentiality before, during, and after the trial. A clinical trial coordinator will be responsible for monitoring the study’s progress and the data’s completeness.

#### Patient and public involvement

A parent representative provided feedback resulting in minor revisions of the parent information material and consent forms before trial initiation (Online Supplement, Appendices B and C). A parent representative will also be involved in the dissemination plans of the trial. However, parents were not involved in the study design and will not be involved in recruiting or data collection during the study.

#### Sample size estimation and inclusion timeline

The sample size was calculated according to the primary outcome. Previous studies on preterm infants born before 30 gestational weeks report a frequency of invasive ventilation after the LISA procedure from 33%^26^ and 41%^27^ up to 75%.^28^ Based on the incidence of invasive ventilation following LISA, we anticipate that the primary outcome will have an incidence of around 45% in the fentanyl group in our trial. Considering an alpha of 0.05 and a power of 0.8 to detect an anticipated incidence of about 30% for the saline group, this trial will enrol 324 infants in a 1:1 ratio. Based on an article by Wiingreen et al., ~123 infants are born before 30 gestational weeks each year in Denmark with the need for surfactant.^29^ The inclusion will last three to four years, considering an expected inclusion rate of 80%.

#### Statistical methods

Baseline characteristics will be presented for each group in the trial population. Categorical variables will be presented as frequencies (counts and percentages). Continuous variables will be presented as medians with interquartile ranges [IQR] or as means with standard deviations [SD].

The primary analysis will use the intention-to-treat principle. A secondary analysis will use the per-protocol principle and exclude infants if they receive additional analgesics associated with the procedure.

The primary outcome will be reported as frequencies (counts and percentages) per treatment group with unadjusted absolute risk difference and relative risks with 95% confidence intervals (CI). The number needed to treat for benefit or harm will be reported if the results of the primary analyses show a statistically significant difference between the two exposure groups.

Secondly, a logistic regression model will be performed adjusting for inclusion site and gestational age (<28 weeks vs more than 28 weeks) and the following independent covariates, which are predictors of assisted ventilation and length of ventilation:^30^ repeat doses of prenatal corticosteroids, 5-min APGAR scores, sex, admission illness severity (according to the Score for Neonatal Acute Physiology/SNAP score^31^), oxygenation index, and small-for-gestational-age status.^32^

All secondary dichotomous outcomes will be described and analysed per the same strategy as the primary outcome. At the same time, mean and percentage differences will be calculated for continuous outcomes.

All analyses will be conducted by use of the statistical software R Studio. Two-sided P values less than 0.05 will be considered statistically significant.

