### Population

Infants will be eligible for inclusion if they are born before 30 gestational weeks at one of the trial sites and meet the criteria for first-choice surfactant treatment by LISA as described by Sweet et al.^4^: worsening babies with RDS and FiO_2_ > 0.30 on CPAP pressure ≥6 cm H_2_O. The primary respiratory support is CPAP in all four units.

Infants will be excluded if they meet any of the exclusion criteria; 1) suspicion of lung hypoplasia, 2) endotracheal intubation at any time before randomisation, 3) suspicion of pneumothorax, pulmonary haemorrhage or pleural effusion before LISA, 4) major congenital anatomical anomalies as described by the European Surveillance of Congenital Anomalies (EUROCAT).^16^

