### Randomisation

Participants will be randomly assigned to the saline or fentanyl group in a 1:1 ratio using computer-generated random allocation sequences with permuted blocks of varying sizes (two and four). The randomisation sequence will be stratified by trial site and gestational age at birth (more or less than 28 completed gestational weeks). Once randomised in the Research Electronic Data Capture (REDCap) system, all entry data will automatically be transferred to the electronic case record forms (eCRF) linked to the infant’s unique identification number. The allocation sequence is pre-coded and generated from the randomisation programme. A person not involved in the trial will generate the allocation sequence. The clinical staff will enrol participants.

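### The primary risk difference and relative risk leave out the stratification factors, so their confidence intervals are wider than need be to the extent that site or gestational age predicts invasive ventilation

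*Protocol article*

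**What the plan says.** On allocation, the protocol article (Randomisation) states: "The randomisation sequence will be stratified by trial site and gestational age at birth (more or less than 28 completed gestational weeks". Allocation within strata uses "permuted blocks of varying sizes (two and four" infants per block, so the arms are held close to equal in every stratum.

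On analysis, the article (Statistical methods) states: "The primary analysis will use the intention-to-treat principle". The primary outcome is then given "per treatment group with unadjusted absolute risk difference and relative risks with 95% confidence intervals (CI". The stratification factors enter only afterwards: "Secondly, a logistic regression model will be performed adjusting for inclusion site and gestational age (<28 weeks vs more than 28 weeks", together with six more covariates (repeat prenatal corticosteroids, 5-minute Apgar score, sex, SNAP score, oxygenation index and small-for-gestational-age status). Secondary dichotomous outcomes follow the same strategy. The article gives no reason for leaving the stratification factors out of the primary analysis.

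**The concern.** Blocking within strata prevents chance imbalance in site and gestational age, so these factors add almost nothing to the true variability of the treatment contrast. The usual standard error for two independent proportions does not know this and still includes the between-stratum part. If the strata carry different risks, the reported interval is wider than the design warrants and the test rejects less often than its nominal 5% under the null.

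At stake is precision already paid for in the randomisation. It matters here for two reasons. The Discussion concedes that the assumed incidences may leave the sample size inadequate. It also frames the hypothesis as one of no difference, and after a null result readers rely mainly on the width of the interval.

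**Working it through.** **Inputs from the article.** Fentanyl group: "incidence of around 45% in the fentanyl group in our trial". Saline group: "to detect an anticipated incidence of about 30% for the saline group". Two-sided alpha 0.05, power 0.80, 324 infants 1:1, so n = 162 per arm. The strata are site by two gestational-age classes. Population says "The primary respiratory support is CPAP in all four units", which gives 4 × 2 = 8 strata; the Discussion expects more sites.

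**Step 1: reproduce the plan's figure.** Let d = 0.15. The sum of the arm variances is 0.45 × 0.55 + 0.30 × 0.70 = 0.4575. The pooled null counterpart is 2 × 0.375 × 0.625 = 0.46875.

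- Pooled: (1.960 × √0.46875 + 0.842 × √0.4575)² / 0.0225 = 162.3, so 163 per arm, 326 in total.
- Unpooled: (1.960 + 0.842)² × 0.4575 / 0.0225 = 159.6, so 160 per arm, 320 in total.
- Power at 162 per arm (pooled test): 79.9%.

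The stated 324 lies between the two totals. It was evidently set for the unadjusted comparison.

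**Step 2: remove the between-stratum part.** Assume two gestational-age classes of equal size, a risk gap g between them, the same 15-point treatment difference in both, and no site effect. Averaged over the classes, p(1 − p) falls by g²/4 in each arm, so:

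- true variance of the difference = (0.4575 − g²/2) / 162; the unadjusted formula uses 0.4575 / 162
- excess width = √[0.4575 / (0.4575 − g²/2)] − 1
- true alpha of the unadjusted test = 2 × {1 − Φ(1.96 × √[0.46875 / (0.46875 − g²/2)])}
- power = Φ((0.15 − 1.96 × SE under the null) / true SE), where the null SE is √(0.46875/162) unadjusted and √[(0.46875 − g²/2)/162] adjusted
- equivalent extra infants = 324 × [0.4575 / (0.4575 − g²/2) − 1]

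For g = 0.30, the true variance sum is 0.4575 − 0.045 = 0.4125. The half-width falls from 1.96 × √(0.4575/162) = 10.4 points to 1.96 × √(0.4125/162) = 9.9 points, a ratio of 1.053.

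| Assumed gap g (points) | Half-width unadjusted / adjusted (points) | Unadjusted wider by | True alpha, unadjusted | Power unadjusted / adjusted | Equivalent extra infants |
|---|---|---|---|---|---|
| 0 | 10.4 / 10.4 | 0% | 5.0% | 79.9% / 79.9% | 0 |
| 10 | 10.4 / 10.4 | 0.6% | 4.9% | 80.0% / 80.3% | 4 |
| 20 | 10.4 / 10.2 | 2.3% | 4.5% | 80.4% / 81.6% | 15 |
| 30 | 10.4 / 9.9 | 5.3% | 3.9% | 81.1% / 83.8% | 35 |
| 40 | 10.4 / 9.5 | 10.1% | 3.1% | 82.2% / 86.8% | 69 |

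**Step 3: check by simulation.** Trials of 324 infants were simulated in 4 sites × 2 classes (equal expected size) with blocks of 2 and 4, 6,000 runs per setting. The unadjusted Wald interval was compared with the Mantel-Haenszel risk difference. The stratum risks are again assumptions.

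| Gestational-age gap / site range (points) | Mean full CI width, unadjusted vs adjusted (points) | Power | Type I error |
|---|---|---|---|
| 0 / 0 | 20.8 vs 20.8 | 80.4% vs 80.2% | 5.3% vs 5.4% |
| 20 / 10 | 20.8 vs 20.3 | 81.3% vs 82.4% | 4.6% vs 5.0% |
| 30 / 20 | 20.8 vs 19.4 | 82.0% vs 85.2% | 4.0% vs 5.4% |

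The simulation error on a 5% rate is √(0.05 × 0.95 / 6000) = 0.28 points, so the 5.3% and 5.4% entries are compatible with 5%. The simulation agrees with the formulas. It also shows that adjusting costs essentially nothing when the strata do not predict outcome.

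**The case against.** The strongest reply is that the planned analysis is valid and delivers what was promised. The sample size was set for the unadjusted test, which keeps about 80% power or slightly more in every setting above. Its type I error is at or below 5%. Both stratification factors are already in a prespecified model. The whole effect depends on how far the strata predict outcome, which the article does not quantify, and at gaps of 10 points or less it is negligible. All of this stands, and it limits the point to efficiency.

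Three stronger readings are tempting and are not supported:

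- A reader might infer that the primary interval is certainly too wide. Without stratum rates the documents cannot show that; the statement is conditional.
- A reader might infer that the trial loses power against its plan. It does not; power is forgone only relative to an adjusted analysis of the same data.
- A reader might infer that the only stratum-adjusted result will be an odds ratio, and so not comparable with the primary estimate. The article names no effect measure for the logistic model, and results could be standardised to risks.

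What the reply does not remove is that the article itself fixes the unadjusted estimate as primary, without giving a reason. It is also plausible that the strata matter: the investigators chose both factors for stratification and again for adjustment, and the Interventions section leaves standard pre-procedure care to differ between sites.

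**Conclusion.** The point holds as a conditional, modest gain in efficiency. If site or gestational age predicts invasive ventilation within 24 hours, the unadjusted 95% interval is wider than it need be and the test is conservative. Over assumed gestational-age gaps of 0 to 40 points, the excess width is 0 to about 10% and the forgone power 0 to about 5 points. At gaps of 20 and 30 points the excess width is about 2% and 5%, worth roughly 15 and 35 infants. These figures rest on equal class sizes, a constant 15-point treatment difference and the design rates of 45% and 30%; none of the stratum risks comes from the article. The validity of the primary analysis is not in question.

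**What to change.** Make the primary estimate a risk difference and relative risk adjusted for site and gestational-age stratum. Two suitable ways are Mantel-Haenszel estimates with the Cochran-Mantel-Haenszel test, or standardisation from a logistic model containing only these two factors and treatment. Name one of them in advance as deciding the primary comparison, and report the unadjusted figures alongside.

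Because more sites are expected, prespecify a rule for pooling very small site strata before unblinding. Keep the fuller covariate model as supportive, and state that it will be reported as a risk difference and relative risk so that it can be read against the primary estimate. Carry the same choice through to the secondary dichotomous outcomes, which follow the primary strategy.

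The cost is a change of analysis wording plus the pooling rule. No new data and no more infants are needed, and nothing material is lost if the strata prove not to be prognostic.

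### The adjusted logistic model reduces gestational age to a 28-week split although gestational age at birth is collected; a continuous term would add a little power to that secondary analysis

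*Protocol article*

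**What the plan says.** The primary outcome is first reported with "unadjusted absolute risk difference and relative risks with 95% confidence intervals (CI" (Statistical methods). The adjusted model comes after that: "Secondly, a logistic regression model will be performed adjusting for inclusion site and gestational age". Its gestational age term is written out as "gestational age (<28 weeks vs more than 28 weeks"), so the functional form is stated and is binary. Six further covariates enter because they predict assisted ventilation: repeat antenatal steroid doses, 5-minute Apgar score, sex, SNAP score, oxygenation index and small-for-gestational-age status. Dichotomous secondary outcomes follow the same strategy.

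The Data collection section states: "Baseline characteristics will include infant gestational age at birth". It does not say whether age is held in weeks or in weeks and days.

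The model term mirrors the randomisation, which is "stratified by trial site and gestational age at birth (more or less than 28 completed gestational weeks").

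**The concern.** Eligibility covers all births before 30 weeks. With one indicator, the model gives a 23-week and a 27-week infant the same gestational age risk, and likewise infants in the 28th and 29th weeks. If the risk of invasive ventilation falls steadily with gestational age, the indicator misses the gradient within each half. The other covariates are there to capture prognosis, so cutting down a likely strong predictor works against the model's own purpose. What is at stake is some efficiency in the adjusted analysis, and some adjustment for chance imbalance within the two broad strata.

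There is also a gap in the wording. Read literally, the model's two categories leave out an infant at exactly 28 weeks. The Randomisation section refers to completed weeks, so a literal reading there leaves out everyone from 28+0 to 28+6.

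**Working it through.** **1. The plan's own figure.** The inputs are from the sample size section: "the primary outcome will have an incidence of around 45% in the fentanyl group", "an anticipated incidence of about 30% for the saline group" and "Considering an alpha of 0.05 and a power of 0.8". The test is two-sided with 1:1 allocation. With pooled variance and no continuity correction, and a mean rate of 0.375:

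n per arm = [1.960 × √(2 × 0.375 × 0.625) + 0.842 × √(0.45 × 0.55 + 0.30 × 0.70)]² / 0.15² = (1.342 + 0.569)² / 0.0225 ≈ 162.3, so 163 per arm, or 326 in total.

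The plan's 324 is reproduced to within two infants. Power at 162 per arm is 79.9%. No covariate enters this calculation. Expected events are 162 × 0.45 + 162 × 0.30 = 72.9 + 48.6 = 121.5.

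**2. Information kept by the split.** This is the squared correlation between continuous gestational age and the 28-week indicator. For a uniform distribution with a proportion p at or above 28 weeks, it equals 3p(1 − p). For a normal distribution split at its median, it is 2/π. The article gives no gestational age distribution, so all of these are assumptions.

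| Assumed distribution | Kept | Lost |
|---|---|---|
| Uniform 26–30 weeks (p = 1/2) | 0.75 | 25% |
| Uniform 25–30 (p = 2/5) | 0.72 | 28% |
| Rising triangular 24–30 | 0.71 | 29% |
| Rising triangular 23–30 | 0.68 | 32% |
| Uniform 24–30 (p = 1/3) | 0.67 | 33% |
| Normal, split at median | 0.64 | 36% |
| Uniform 23–30 (p = 2/7) | 0.61 | 39% |

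**3. Effect on power.** Logistic models were fitted to simulated trials of 324 infants. Allocation was balanced within the 28-week strata, marginal rates were 45% and 30%, and there were 4,000 runs per scenario. The odds ratio per week earlier is assumed. "Continuous" means a linear term in place of the split.

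| Distribution | OR per week | Unadjusted | Split | Continuous | Gain over split (points) |
|---|---|---|---|---|---|
| Uniform 24–30 | 1.2 | 80.5% | 80.9% | 81.1% | 0.2 |
| Uniform 24–30 | 1.5 | 81.1% | 82.8% | 83.7% | 0.9 |
| Uniform 24–30 | 2.0 | 81.3% | 84.9% | 89.0% | 4.1 |
| Triangular 24–30 | 1.2 | 80.1% | 80.4% | 80.7% | 0.3 |
| Triangular 24–30 | 1.5 | 79.7% | 81.2% | 82.0% | 0.8 |
| Triangular 24–30 | 2.0 | 82.0% | 85.1% | 87.5% | 2.4 |

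The simulation error of each figure is √(0.8 × 0.2 / 4000) ≈ 0.6 points, so gains below one point show direction rather than size. In every row the split model has at least the power of the unadjusted comparison.

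**4. Effect on the interval.** These runs assumed 46% of infants at or above 28 weeks. They compared the mean standard error of the treatment log odds ratio under the split with that under the split plus a continuous term. The results were 0.240 v 0.244, 0.246 v 0.254 and 0.253 v 0.267, at odds ratios of 0.74, 0.64 and 0.55 per additional week. The standard error rises slightly. Power improves because the conditional log odds ratio moves further from zero by more than the standard error grows.

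**5. Overlap with other covariates.** The step 3 simulation leaves out site and the six other covariates. With one prognostic covariate correlated 0.7 with gestational age already in the model, one set of runs found no gain: 82.8% v 82.6% at 0.74 per week, and 86.0% v 85.6% at 0.64. Another set, with correlations of 0.4 to 0.7, still found a gain of about 0.4 to 2 points. The gain shrinks with overlap, but it does not generally vanish.

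**The case against.** The strongest defence is that adjusting for a stratification factor in the form used at randomisation is accepted practice, and the plan does this. Nothing in the plan is contradicted, and the benefit of a continuous term depends on an assumed distribution, assumed effects and the overlap with SNAP, Apgar score and oxygenation index. That stands, and it is why this is a refinement and not an error. It does not defend stopping at the split, because the factor can stay and a continuous term can be added beside it.

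Three stronger readings are tempting, and the article does not support them:

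- **The trial loses planned power.** The headline result is the unadjusted risk difference and relative risk, and the 324 infants were sized on an unadjusted comparison. The form of a covariate in the later model cannot change either.
- **A third of the information is lost.** That figure lies within the 25% to 39% range, but it describes the covariate and not the treatment comparison, and no distribution is given to fix it.
- **The interval would narrow.** For a logistic odds ratio it does not (step 4).

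The boundary wording is an editorial matter. The Blinding section has the stratification variables entered in REDCap before randomisation, so each infant should have a recorded stratum whatever the article's phrasing.

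**Conclusion.** The point holds as a minor efficiency improvement to the adjusted analysis. The split discards roughly 25% to 39% of the linear information in gestational age. That leaves the adjusted treatment test about 0.2 to 1 point less powerful than it could be for a weak to moderate gestational age effect (odds ratio 1.2 to 1.5 per week), and about 2 to 4 points less for a strong one (2.0). Overlap with the other covariates reduces these figures. All of them rest on assumed distributions and a linear effect on the logit, neither of which the article supplies. The unadjusted primary analysis, the sample size and the planned 80% power are untouched, and the trial's conclusion is not threatened.

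**What to change.** In Statistical methods, keep the stratification factor exactly as used at randomisation, and state in both sections which category infants at 28 weeks belong to (for example <28+0 versus ≥28+0, if that is how REDCap assigns them). Add gestational age at birth as a continuous term, linear or as a restricted spline, in weeks and days if recorded that way. Apply it to the adjusted models for the primary and the dichotomous secondary outcomes. Specify the form before unblinding, so that it cannot appear to have been chosen on the result. Leave the unadjusted primary estimate as it is.

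The cost is a change of wording: no extra infants and no new data item. The model gains one degree of freedom for a linear term, or two to three for a spline, against about 120 expected primary events. Rarer secondary outcomes have fewer events, and the linear term is the safer choice there.

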## Discussion

This randomised controlled trial compares infants exposed to the LISA procedure with pre-procedure fentanyl or placebo (isotonic saline) by the risk of invasive ventilation, meaning mechanical or manual ventilation via an endotracheal tube, for at least 30 min (cumulated) within 24 h of the procedure. All infants will receive standardised non-pharmacological comfort care before and during the LISA procedure (Online Supplement, Appendix A). In this trial, we plan to test the hypothesis that there is no difference between the need for invasive ventilation within 24 h of the LISA procedure performed with or without pre-procedure analgesia (i.e., fentanyl).

The LISA procedure is performed worldwide without consensus regarding non-pharmacological and pharmacological approaches. There is clinical equipoise regarding the positive and negative effects of pharmacological analgesic treatment when performing the LISA procedure. There is a delicate balance between the desired effect of reduction in pain and discomfort and the risk of over-sedation and apnoea requiring positive pressure ventilation.^11,12^ Comfort and pain relief using a non-pharmacological approach has yet to be thoroughly investigated in the context of LISA and how it compares with pharmacological analgesic treatment. Some studies indicate that a non-pharmacological approach, including facilitated tucking,^33^ swaddling,^34^ and skin-to-skin care^35^ compared to pharmacological analgesic treatment, may reduce the incidence of apnoea and, ultimately, the use of invasive ventilation,^20,21^ while achieving the same level of comfort. Hence, some centres make the first LISA attempt without any premedication, as studies report that the LISA procedure is generally well tolerated without analgesia,^1,36,37^ especially in preterm infants.^38^ Therefore, some studies advise using pharmacological agents only if non-pharmacological methods are insufficient to ensure patient comfort.^39^ It is essential to investigate pharmacological and non-pharmacological approaches to reduce pain, discomfort, and adverse effects due to medication during neonatal procedures, including the LISA procedure, as the insertion of a laryngoscope and intratracheal administration of surfactant obviously contradicts the term “less invasive”.^40^

As a safety precaution in the NONA-LISA trial, the staff will continuously monitor the infant’s level of discomfort or pain during the procedure by an objective score (modified COMFORTneo). The COMFORTneo score is the national standard for assessing pain and discomfort in newborns. Most NICU nurses are COMFORTneo certified. Previous studies have demonstrated the ability of the COMFORTneo score to assess pain and discomfort during the LISA procedure.^20,21^ However, the COMFORTneo score formally requires a two-minute assessment of the infant and was not designed for intra-procedure assessments as planned in the NONA-LISA trial. To avoid interrupting the procedure flow, performing the score over 2 min is not feasible. Thus, intra-procedure assessments of COMFORTneo in this trial will be based on the standard COMFORTneo items assessed faster than 2 min. The use of COMFORTneo in this trial is described in detail in Online Supplement, Appendix A. Importantly, if the modified COMFORTneo score is ≥14 during the procedure, the procedure may be paused, and non-pharmacological measures must be improved. If improved non-pharmacological measures are ineffective, the team may opt for open-label fentanyl administration. The infant will still be given the highest level of care and attention by the staff.

This trial has certain limitations. The pragmatic design of this trial allowing fentanyl dosages between 0.5–1.0 mcg/kg will imply difficulty interpreting the specific results, as this trial will not have the necessary power to determine causality between an exact dosage of fentanyl and adverse events (e.g., apnoea). Despite this, a pragmatic design was necessary to ensure participation from all feasible Danish trial sites. As the dosing interval reflects clinical practice, it ensures generalisability and relevance for neonatal intensive care outside trial settings.

Non-pharmacological measures in neonatal care are complex and multifactorial, where all factors are relevant for the potential success of the intervention. Several studies have shown synergy when combining several non-pharmacological measures. However, there is no evidence favouring one specific approach. This study will use a protocolised non-pharmacological approach to standardise the treatment across inclusion sites.

The incidence of invasive ventilation following LISA varies significantly in other studies, and the anticipated incidences in the fentanyl and saline groups may cause an inadequate sample size to achieve the necessary power. However, compared to ongoing clinical trials like PRELISA (NCT05065424), we expect to include more than five times as many infants in the NONA-LISA trial. Other trials like the PROLISA (NCT04016246) include more infants but compare propofol to placebo.

The NONA-LISA trial received approval for deferred consent, which may significantly improve the inclusion rates. Nevertheless, with all the Danish NICUS as inclusion sites, the inclusion period will last up to four years, making the NONA-LISA trial vulnerable to changes in best practices regarding surfactant treatment. We expect to include other trial sites.

